## Abstract

Little valid information is available on human milk nutrient concentrations, especially for micronutrients (MNs), and there are no valid reference values (RVs) across lactation. In this multi-center collaborative study, RVs will be established for human milk nutrients across the first 8.5 mo postpartum. Well-nourished, unsupplemented women in Bangladesh, Brazil, Denmark, and The Gambia (*n* = 250/site) were recruited during the third trimester of pregnancy. Milk, blood, saliva, urine, and stool samples from mothers and their infants are collected identically at 3 visits (1–3.49, 3.5–5.99, 6.0–8.49 mo postpartum). Milk analyses include macronutrients, selected vitamins, trace elements and minerals, iodine, metabolomics, amino acids, human milk oligosaccharides, and bioactive peptides. We measure milk volume; maternal and infant diets, anthropometry, and morbidity; infant development, maternal genome, and the infant and maternal microbiome. RVs will be constructed based on methods for the WHO Child Growth Standards and the Intergrowth-21st Project. This trial was registered at clinical trials.gov as NCT03254329.

## Introduction

For the first 6 mo of life, the WHO recommends exclusive breastfeeding (EBF) (1). However, human milk is not only essential for optimal infant health and development during the first 6 mo, but it can also be an important source of nutrients and other factors for the following ≈18 mo (2), yet we lack valid information on its nutrient content (3, 4), especially for micronutrients (MNs). Many human milk MN concentrations are much lower where women consume poor diets (5, 6), including MNs of major public health importance, such as vitamin A, thiamin (B-1), B-12, and iodine (7–9). These low milk concentrations caused by maternal deficiency and/or low intake have documented adverse effects on infant health and development (10), e.g. growth faltering and developmental delays have been linked to low milk concentrations in conjunction with severe maternal-infant deficiencies of vitamin B-12, B-1, B-6, D, iodine, and choline (9, 11).

In 2006, the new WHO International Child Growth Standards exposed that growth faltering starts shortly after birth with a much higher prevalence during the first 6 mo than previously assumed (12). During the same timeframe for infancy, the high prevalence of MN deficiency has been reported in exclusively or predominantly breastfed infants (6), e.g. thiamin status in Cambodia, which expands to mothers and milk, and low status of several MNs in Bangladesh (13, 14), suggesting poor milk quality could contribute to the growth faltering and MN deficiency.

The last and only global data on milk composition with a focus on MNs were collected in the 1985 WHO Collaborative Study on Breast-Feeding, over 30 y ago, with limited data collection (15). Our recent literature review on human milk revealed the general lack of a systematic sample collection and of appropriate consideration of factors affecting milk nutrient concentrations, e.g. stage of lactation, maternal nutritional status and diet, or smoking and alcohol use, among others (4, 16, 17). Moreover, inadequate methods for analyzing nutrients in the human milk matrix and lack of reported validation data added to the unreliability of many past reports (3, 18). Therefore, the literature on human milk composition is very difficult to interpret and practically impossible to use for the purposes for which such information is needed.

Due to all these limitations, there are no adequately established reference values (RVs) for nutrient concentrations in milk, and recommended nutrient intakes of infants, young children, and lactating women are based on many unvalidated and incorrect estimates of milk MN concentrations. Given the lack of RVs there is no benchmark against which to evaluate human milk quality in different populations, or the possible need for or effects of nutrient interventions on human milk MNs.

The primary study outcome and analysis objective of the Mothers, Infants, and Lactation Quality (MILQ) Study is the construction of reference ranges for values of vitamin and mineral concentrations in human milk from well-nourished mothers and their healthy infants. The reference range curves, between the 2.5 and 97.5 percentiles, will be constructed between 1 and 8.5 mo by combining data from the 4 study sites, using nutrient and volume data from milk samples obtained from each mother during 3 visits postpartum. This article describes the methodologies and protocols implemented for conducting the MILQ Study.

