### Statistical analysis

#### Sample size calculations

Since the primary outcome is estimated key centiles of the distributions of nutrient concentrations in human milk, and centiles are invariant to monotonic transformation, sample sizes for constructing RVs are based on: *1*) estimating the 50th and 5th percentiles of each breast milk nutrient across time periods within each site and *2*) being able to establish equivalency among study sites before pooling data.

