#### Estimating centiles

We aim for a monotonic transformation for each variable across all study sites to attain normal (Gaussian) distribution, from which parametric estimates of the centiles will be constructed. Regression models will be used to estimate the parameters of the distribution at each time period, but since such models will not be determined until the data are available, the sample size is based on a generic estimate for the p^th^ centile:
(1)}{}\begin{eqnarray*} \bar{X} + {Z_p} \times s \times C{F_s} \end{eqnarray*}where:

}{}$\bar{X}$
 = sample mean (or estimated predicted value from the regression model)

*Z_p_* = p^th^ centile of the standard normal distribution (negative for *P* <0.50)

}{}$s$
 = sample SD (or estimated SD from regression model)

*CF_s_* = correction factor for bias of s as an estimator of population SD (negligible for *n* >50).

The SE of this estimate, if *n* is >50, is approximately:
(2)}{}\begin{eqnarray*} \frac{\sigma }{{\sqrt n }}\sqrt {1 + 0.5 \times Z_\alpha ^2} \end{eqnarray*}

The desired width of the CI is based on the distance of the 50th and 5th centiles from neighboring centiles, which yields a sample size invariant to the location, scale, or shape of the underlying distribution, as long as the variable can be normalized. This requires an overall sample size of 255 per time point to avoid overlap between the 95% CIs around the 5th and 10th centiles, and to estimate the sample median within 5 centiles with 95% confidence (**Table 4**). Once the centiles of interest are estimated for the transformed variable, they will be back-transformed to be expressed in the original units.

**TABLE 4 tbl4:** Planned analyses in the Mothers, Infant, and Lactation Quality (MILQ) Study

Analyte Category	Analytes	Milk	Blood	Urine	Stool	Method	Ref.^1^
Fat-soluble	Vitamin A	X	X^P^			HPLC-MWL	(31)
vitamins and carotenoids	Vitamin E						
	α-carotene						
	β-carotene						
	β-cryptoxanthin						
	Lycopene						
	Lutein/zeaxanthin						
	Ergocalciferol (D_2_)	X	X^P^			UPLC-MS/MS	
	Cholecalciferol (D_3_)					CPBA	(32)
	25-OH-D_2_						
	25-OH-D_3_						
Water-soluble vitamins	Thiamin (B-1)	X	X^R^			HPLC-FLD	(33)
	Thiamin monophosphate (B-1)						
	Thiamin diphosphate (B-1)						
	Riboflavin (B-2)	X	X^P,R^			UPLC-MS/MS	(27)
	FAD (B-2)						
	FMN (B2)						
	Nicotinamide (B3)						
	Nicotinic acid (B-3)						
	Nicotinamide mononucleotide (B-3)						
	NAD (B-3)						
	NAD(P) (B-3)						
	Nicotinamide riboside (B-3)						

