**FIGURE 3 fig3:**
[figure not shown]
Hypothetical graphical illustration of reference values that may result for a micronutrient.

For each nutrient and time period, the distribution of the human milk variable will be examined and extreme outliers will be investigated and, if needed, removed. Box–Cox and other transformations will be used to normalize each variable, preferably using the same transformation across study sites, and the Shapiro–Wilk statistic to assess normality; skewness, kurtosis. The general shape of the distribution will also be examined. Parameters will be compared among study sites as described above, and information from the sites will be combined if the sites are deemed to be equivalent, or if differences have no material effect on key percentiles; otherwise, different sets of RV centiles may be constructed per site, or with only 2 or 3 pooled sites.

Parameters from the identified distribution will be estimated from the data, and centiles of interest (5th, 25th, 50th, 75th, 95th) will be estimated for each nutrient based on the theoretical percentiles of the underlying distribution, as described above. Smoothing techniques such as cubic splines will be employed, assuming the centiles follow smooth and continuous functions. Tables and curves of estimated centiles will be created for each nutrient and time period. SAS for Windows Release 9.4 (SAS Institute) will be used for all analyses.

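### The primary outcome is a 2.5th–97.5th percentile range, but the analysis lists only the 5th to 95th centiles and the sample size is argued only for the 5th and 50th

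*Protocol article*

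**What the plan says.** Three parts of the protocol article bear on which centiles are the target.

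- **Introduction, primary outcome.** "The reference range curves, between the 2.5 and 97.5 percentiles, will be constructed between 1 and 8.5 mo", and this is to be done "by combining data from the 4 study sites". The promise is therefore made for pooled data.
- **Data analysis plan (text after Figure 3).** "centiles of interest (5th, 25th, 50th, 75th, 95th) will be estimated for each nutrient". Neither the 2.5th nor the 97.5th is on this list.
- **Sample size calculations and Estimating centiles.** The first stated basis for the sample size is "estimating the 50th and 5th percentiles of each breast milk nutrient across time periods within each site". The precision rule follows: "The desired width of the CI is based on the distance of the 50th and 5th centiles from neighboring centiles". There are two criteria. One is given as "This requires an overall sample size of 255 per time point to avoid overlap between the 95% CIs around the 5th and 10th centiles". The other concerns the median, which should be known to within 5 centile points at the same confidence level. Nothing is said about the 2.5th or 97.5th.

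The Data analysis plan also keeps a fallback: reference values for single sites, or for two or three pooled sites, if the four cannot be combined. The Discussion says that the number per site is enough for site-specific values.

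**The concern.** The limits of the reference range are what this study exists to produce. The Discussion presents the values as benchmarks for milk quality and as a basis for revisiting intake recommendations, so the limits decide which milk is called low or high. An analyst who follows the Data analysis plan as written would produce a 5th–95th range, and the range named as primary would not appear. At the lower end the choice decides whether 5% or 2.5% of milk from healthy, well-nourished mothers falls below the limit. If the pair is not fixed in advance, it can be chosen after the data are seen.

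A second question follows. The precision argument was made for the 5th centile, and the standard error grows towards the tails. A reader needs to know what the planned numbers deliver at the 2.5th, both pooled and for the single-site fallback.

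**Working it through.** **Inputs, all from the protocol article.** Limits 2.5/97.5 (Introduction); listed centiles 5, 25, 50, 75, 95 (Data analysis plan); 255 per time point (Estimating centiles); 250 per site and time period, so 4 × 250 = 1000 pooled; standard error of a centile from formula (2), σ/√n × √(1 + 0.5 Z²).

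**Notation.** In SD units on the transformed scale, let k(p) = √(1 + 0.5 z_p²), so that SE = k(p)/√n.

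| Centile | z_p | k(p) |
|---|---|---|
| 2.5th | −1.960 | 1.709 |
| 5th | −1.645 | 1.534 |
| 10th | −1.282 | 1.350 |

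**1. Reproduce the 255.** With multiplier c for the 95% interval, two intervals do not overlap when n ≥ [c (k₁ + k₂)/(z₂ − z₁)]².
- 5th against 10th, gap 0.363: c = 1.96 gives [1.96 × (1.534 + 1.350)/0.363]² ≈ 242; c = 2 gives 252.
- Median within 5 centiles, z(0.55) = 0.1257: (1.96/0.1257)² gives 244 after rounding up; c = 2 gives 254.

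The stated 255 is recovered closely with c = 2 and is slightly conservative with 1.96. The method is therefore understood.

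**2. Size of the discrepancy in limits.** The limits are ±1.960 SD or ±1.645 SD, a difference of 0.315 SD at each end. The share outside is 2 × 2.5% = 5% or 2 × 5% = 10%. Among 1000 mothers that is 50 or 100.

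**3. Precision at the 2.5th centile.** The half-width is 1.96 × 1.709/√n. The end points are converted back to centiles of the normal distribution.

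| n per time point | Half-width for 2.5th (SD) | 95% interval, 2.5th | 95% interval, 5th |
|---|---|---|---|
| 250 (one site) | 0.212 | 1.49th to 4.02nd | 3.33rd to 7.29th |
| 500 (two sites) | 0.150 | 1.74th to 3.51st | 3.76th to 6.55th |
| 1000 (four sites) | 0.106 | 1.94th to 3.19th | 4.09th to 6.06th |

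By symmetry the same holds at the 97.5th.

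**4. What n the 2.5th would need.** The article sets no criterion for it, so each line below is an assumption.
- Neighbour 7.5th (the plan's own 5-point gap): 140 (c = 1.96) to 146 (c = 2).
- Same standard error as the 5th has at n = 255: 255 × (1.709/1.534)², which is 317.
- Neighbour 5th (the nearest centile the plan reports): [1.96 × (1.709 + 1.534)/0.315]² ≈ 407; c = 2 gives 424.

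One site of 250 meets the first and misses the other two. Two pooled sites (500) and four (1000) meet all three.

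**The case against.** The strongest reply is that nothing of substance is missing. The plan normalizes each nutrient and reads centiles from the fitted distribution, so the 2.5th and 97.5th need only a different Z in formula (1). That stands, and it makes the remedy cheap. It does not settle which pair is the primary range. Nor can an analysis plan that is not shown here: the article states two different pairs, and a further document could confirm only one of them.

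A reader might go further and infer that the study is too small for the 2.5th centile, that the plan's own criterion fails there, that 407 per time point is required, or that single-site values must stop at the 5th and 95th. The article does not support these readings, for three reasons.
- The 2.5th–97.5th curves are promised for the pooled sites, where precision is adequate under every criterion tried.
- The plan's criterion compares centiles 5 points apart. Setting the 2.5th against the 5th halves that gap. With a 5-point gap, 250 is enough.
- On the centile scale, the single-site interval for the 2.5th is narrower (about 2.5 points) than the one accepted for the 5th (about 4 points).

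What remains is more modest. The Discussion's assurance about site-specific values rests on a calculation made only for the 5th and 50th, so it cannot be carried over to the 2.5th without a stated criterion.

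**Conclusion.** The inconsistency is real and concerns the definition of the primary outcome. The Introduction promises 2.5th–97.5th, the Data analysis plan would deliver 5th–95th, and the sample size speaks only to the 5th and 50th. The consequence is 5% or 10% of the reference population outside the range, or 0.315 SD at each limit. This conclusion comes from the text alone and needs no assumption about precision.

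The pooled plan is precise enough for the 2.5th and 97.5th. For a single site the answer is open: the requirement runs from about 140 to 424 per time point, depending on the criterion. These figures assume that the transformation achieves normality, that formula (2) holds in the tails, and that all 250 mothers per site contribute at each time point. Fewer usable samples would widen the intervals.

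**What to change.** Use one pair of limits throughout, in one of two ways.

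1. **Keep 2.5th–97.5th as primary.** Add both centiles to the list in the Data analysis plan. State their precision from formula (2): about the 1.9th to 3.2nd centile for the lower limit with 1000 pooled, and about the 1.5th to 4.0th for one site of 250, with the mirror image at the upper limit. Add to the sample size section and the Discussion that the per-site justification was worked out only for the 5th and 50th. If a caveat on single-site values is wanted, name the criterion and give the range (140–146, 317, or 407–424 per time point), not one fixed number.
2. **Make 5th–95th primary.** Restate the range in the Introduction. The list of centiles and the sample size argument then stand as they are.

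Either way the cost is a few sentences. Recruitment, sampling and the fitted models do not change. The choice should be recorded before the reference values are constructed.

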## Methods

### Study design and settings

The MILQ Study is a multi-center, collaborative project with data and sample collection in 4 countries, Bangladesh, Brazil, Denmark, and The Gambia. Samples and data (e.g. anthropometry, questionnaires) are collected from 250 mother-infant dyads per country site (*n *= 1000 mothers and 1000 infants) in a systematic, identical way across sites for colostrum (1–2 d postpartum), and at 3 subsequent time points: 1.0–3.49 mo (visit 2), 3.5–5.99 mo (visit 3), and 6.0–8.5 mo (visit 4) postpartum (*n* = 1000 dyads). Within each time window the collection of samples is randomized so that some samples and data are available for almost every day between 1 and 8.5 mo postpartum, enabling smoothing of reference curves. Visits 2 through 4 are divided into 3- or 4-wk time periods. If a participant's first visit is randomly assigned to the first week of a time period, then their second and third visits are also scheduled in the first week of the time block. To evaluate the effect of intraperson variability on outcome variables, a subset of 50 women in Bangladesh, Brazil, and The Gambia are providing a second milk sample on visits 2 and 3. Details about each study location and analytical site are provided in **Tables 1** and **2**.

**TABLE 1 tbl1:** Study settings, and participant information in the Mothers, Infants, and Lactation Quality (MILQ) Study

	Bangladesh	Brazil	Denmark	The Gambia
Location	Mirpur (periurban area of Dhaka)	Madureira and São Cristóvão (Rio de Janeiro)	Copenhagen Rigshospitalet	Bakau and Fajara urban Gambia near Banjul
Average income, USD/mo	245	456	3120	247
Literacy, %	69	93	100	>65
Maternity leave, mo	6^1^	4–6	9–12	6
EBF, %				
2 mo	_	50	71	70
4 mo	_	_	60	_
6 mo	55	_	_	47
Infant stunting at 6 mo, %	18.6	4.8	<1	9
Usual diet	Rice	Rice and beans	Typical Western diet	Rice and maize
	Fruit and vegetables	Fruit and vegetables	Animal source foods, dairy	Fruit and vegetables
	Some animal source foods	Animal source foods, dairy		Groundnuts
		Pasta, high-processed foods		Some animal source foods
MMN supplementation	No, unless prescribed		Some, but not in this study	No
*Government mandates or recommendations*				
Perinatal	_	_	Iron and folic acid	_
Pregnancy	_	Iron and folic acid	Vitamin D	Iron and folic acid
	_	_	Calcium (low cow milk intake)	_
Fortification programs	No	Iron and folic acid (flour)	Iodine (salt)	No
Facilities	icddr, b, Dhaka	Maternity Hospital Herculano	Hvidovre Hospital	SOS Mother and Child Clinic,
		Pinheiro	Herlev Hospital	Bakoteh
		Municipal Center of Health	Rigshospitalet	
		Ernesto Zeferino Tibau Junir		
Type of informed consent	Written consent by study participant^2^			
Sample storage and use	Sample use is explained and consented to in the informed consent document			
	Samples are available for 5 y	Samples are available for 10 y	Samples are available for 5 y	
	Samples may be used for other projects but may require additional consent			Samples may be used for other projects
Deidentification and data security	All data is collected by study ID only into a secure database, at which point it cannot be linked back to the study participants			
	Separate, password-protected participant log is maintained by research team			
Compensation	Free treatment of any conditions by study physician	Travel costs	Breastfeeding counseling by phone, if desired	Travel costs
		Breastfeeding counseling	A small gift for the infant upon study completion	
Follow-up	If needed, referrals are provided to government specialized hospitals for further management	If needed, determined by study nurse, referrals are provided to specialized care facilities for further management^3^	A medically trained person is available for participants experiencing any illness, or if any abnormal test results	If needed, determined by study nurse, referrals are provided to MRCG@LSHTM, Fajara, clinic for further management

1 For government employees, varies for private entities.

2 If women are unable to read the consent form, it is read to them in their mother tongue and full informed consent is confirmed by *1*) the research staff (Bangladesh, Brazil), and *2*) by a literate, independent witness (The Gambia).

3 Issues related *1*) to illness: public Basic Health Unit, *2*) to breastfeeding issues: human milk bank at study site, *3*) to depression: Psychiatric Institute at the University. EBF, exclusive breastfeeding; icddr, b, International Centre for Diarrhoeal Disease Research, Bangladesh; MRCG@LSHTM, The MRC Unit The Gambia at the London School of Hygiene and Tropical Medicine; MMN, multiple micronutrients; PI, principal investigator; USD, US dollars.

**TABLE 2 tbl2:** Analytical sites of the Mothers, Infant, and Lactation Quality (MILQ) Study

Site	Analyses
USDA, ARS-WHRNC^1^	Macro- and micronutrients, and metabolomics
	Selected micronutrients in colostrum based on available volume
	Microbial community of infant stool by 16s rRNA sequencing
	Shotgun metagenomics sequencing of infant stool based on 16s rRNA
	Screening, DNA quality/quantity, and availability of other data
	Milk cell mRNA transcriptome
	Maternal genetic and epigenetic signatures (buffy coat)
UC Davis, USA^2^	Human milk oligosaccharides and proteomics
ETH Zürich^3^	Iodine and iodine status biomarkers
St. John's Medical College^4^	Milk volume by D_2_O saliva analyses
University of Cambridge, UK^5^	Vitamin D in human milk

1 USDA, Agricultural Research Service-Western Human Nutrition Research Center, Davis, CA, USA.

2 University of California, Davis, CA, USA.

3 Eidgenössische Technische Hochschule, Zürich, Switzerland.

4 Bengaluru, India.

5 Nutritional Biomarker Laboratory, MRC Epidemiology Unit, University of Cambridge, Cambridge, UK.

D_2_O, deuterated water.

### Inclusion criteria

Participant's inclusion and exclusion criteria vary across the study periods but are focused mainly on the nutritional status and health of the mother and infant, and the requirement for EBF during the first 3.5 mo postpartum. Detailed information about the inclusion and exclusion criteria are provided in **Table 3**.

**TABLE 3 tbl3:** Inclusion and exclusion criteria in the Mothers, Infants, and Lactation Quality (MILQ) Study

	Bangladesh	Brazil	Denmark	The Gambia
Recruitment	Directly by local research team	Invitation letter to meet	Directly by local research team	
Enrollment	After delivery		During pregnancy	
*Mothers inclusion criteria*				
Age, y	18–40			
Height, cm	>145	≥150		
BMI, kg/m^2^				
<2 wk postpartum	≥18.5 to ≤30.0	_	_	≥18.5 to ≤30.0
Prepregnancy		≥18.5 to ≤30.0	≥18.5 to ≤30.0	
MUAC, cm	≥23 to ≤ 33	_	_	≥23 to ≤33
Hemoglobin,^1^ g/L	>100	>100	No reported anemia	>100
Maternal health	No relevant past or current medical problems (e.g. gestational diabetes, pre-eclampsia)			
Smoking	No	No	No	No
Alcohol intake, mL	<50	<40	<50	<50
Diet^2^	Nonvegan or macrobiotic diet			
	≥15 g of ≥15 food groups each/d	≥15 g of 4 of 8 food groups/d	≥15 g of ≥15 food groups each/d	
MMN use				
3rd trimester	Iron and folic acid			
			Vitamin D and calcium	
lactation	Iron and folic acid			
			Vitamin D and calcium	
Fortified foods	Low habitual intake of highly fortified foods, expect iodized salt			
Delivery	Singleton			
Weeks of gestation	37–42			
Breastfeeding				
≤3.5 mo	Exclusive breastfeeding			
≤8.5 mo	Partially breastfeeding			
Infant inclusion criteria				
Birthweight, g	2500–4200			
Infant health	No congenital malformations that interfere with feeding or growth and development			
Visit 2 exclusion criteria	Cessation of, or nonexclusive, breastfeeding			
	Serious maternal illness			
	Infant length-, weight-for-age, or weight-for-length <-2 Z			
	Maternal MMN consumption during lactation other than stated above			
Visits 3 and 4 exclusion criteria	Cessation of breastfeeding			
	Infant length-, weight-for-age, or weight-for-length <-2 Z			
	Abnormal infant development based on Ages & Stages Questionnaire (abnormal performance on ≥2 of the 7 domains)			

1 Hemoglobin determined during the third trimester, or by maternal questionnaire in Denmark.

2 Using a locally appropriate and validated FFQ.

MMN, multiple micronutrients; MUAC, midupper arm circumference.

